### Evaluation process

#### Primary and secondary outcomes

The expected primary outcomes of the Spanish intervention were as follows: increases in the consumption of fruits and vegetables and physical activity practice, along with reductions in TV/computer/game console use. The secondary outcomes were as follows: increased breakfast consumption, engagement with local recreation and reduced obesity prevalence. The outcomes of the Spanish intervention were measured by the Health Behaviour in School-aged Children Study (HBSC) Survey 2009–2010 [35] to evaluate the adolescents’ lifestyles at baseline and at the end of the intervention as presented in Table 3. The HBSC study is a validated cross-sectional survey of school students that collects data every four years on 11-, 13- and 15-year-old adolescents [36]. The baseline measurements from the intervention and control groups were performed in the second phase, and the end-of-study measurements were performed in the fourth phase (Fig. 1). Analyses and evaluations of each country’s intervention and global project will be performed in phase 5 (Fig. 1) so that the project can be concluded.

**Table 3 Tab3:** Outcomes measurements in the Health Behaviour in School-aged Children Study (HBSC) Survey

Health Behaviour in School-aged Children Study Items	Outcome measured	Question	Possible answers
Eating habits	Nutritional behaviour. Fruit, vegetable and water consumption.	How many times a week do you usually eat or drink (fruits, vegetables, sweets, coke or other soft drinks that contain sugar)…?	Never, less than once a week, once a week, 2–4 days a week, 5–6 days a week, once a day, every day, every day more than once every day.
(primary outcomes)	Breakfast quantity and quality	How often do you usually have breakfast (more than a glass of milk or fruit juice)?	*Weekdays* (I never have breakfast, one day, two days, three days, four days, five days).
			*Weekends* (I never have breakfast during the weekend, I usually have breakfast on only one day of the weekend (Saturday OR Sunday), I usually have breakfast on both days (Saturday AND Sunday)).
Physical activity	Physical activity practice	Over the past 7 days, on how many days were you physically active for a total of at least 60 min per day?	0 days, 1 day, 2 days, 3 days, 4 days, 5 days, 6 days, 7 days.
(primary outcomes)			

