#### Statistical analysis plan

We estimated that with a sample size of 121 adolescent schoolmates per group, the study will have 90 % power to detect a difference of a 0.5 portion of vegetables or fruits between the intervention and control groups, setting the bilateral level of statistical significance at 5 %. We anticipate a loss of follow-up rate of 30 %.

Analyses of the results will be performed on an intent-to-treat (ITT) basis, defined as a participant who had at least baseline efficacy data.

The descriptive results are expressed as the means ± standard deviations and the 95 % confidence intervals for quantitative variables or as frequency distributions for qualitative variables. Generalised linear mixed models are used to analyse differences between the intervention and control groups and changes in primary and secondary outcomes from baseline to the end of the intervention. For the rest of the efficacy variables, we will use Fisher’s exact test for the categorical variables and Student’s *t*-test for the continuous variables. The significance level is fixed at a bilateral level of 5 %.

All statistical analyses are performed with SPSS version 22.0 (SPSS, Inc., IBM, Armonk, NY, USA).

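### Minor: any remaining efficacy item with ordered HBSC answers would go to Fisher's exact test, which uses neither the category order, the pupil's baseline answer nor the school

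*Protocol article*

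**What the plan says.** The Statistical analysis plan section has two tiers. The first covers the main outcomes: "Generalised linear mixed models are used to analyse differences between the intervention and control groups and changes in primary and secondary outcomes from baseline". Here change is followed up to the closing survey. The second covers everything else: "For the rest of the efficacy variables, we will use Fisher’s exact test for the categorical variables and Student’s" t-test if continuous. The remaining variables are not listed.

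The section on primary and secondary outcomes names the primary outcomes as "increases in the consumption of fruits and vegetables and physical activity practice, along with reductions in TV/computer/game console use" and the secondary outcomes as "increased breakfast consumption, engagement with local recreation and reduced obesity prevalence. The outcomes of the Spanish intervention" (the quote runs on into the next sentence). Neither list contains sweets or soft drinks.

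Table 3 gives the food question: "How many times a week do you usually eat or drink (fruits, vegetables, sweets, coke or other soft drinks that contain sugar". The answers begin "Never, less than once a week, once a week, 2–4 days a week, 5–6 days a week, once a day" and continue to more than once daily, about seven ordered levels. The table heads this block as primary outcomes, but describes what the row measures as "Nutritional behaviour. Fruit, vegetable and water consumption". The survey is given twice, "to evaluate the adolescents’ lifestyles at baseline and at the end of the intervention", so each item has a baseline answer.

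**The concern.** Applied to two arms by about seven ordered levels, Fisher's exact test (in its extension to larger tables) treats the levels as interchangeable labels. Its power is spread over every pattern of difference, whereas a general move up or down the scale is the pattern of interest. It returns a p-value with no direction and no effect size. It has no place for the pupil's baseline answer, and it takes pupils from four high-schools, two per arm, as independent.

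At stake is the reading of some additional survey items. A real shift could be missed, or a significant result could reflect an irregular pattern. Two parts of one survey question, fruit and sweets, could also be analysed in ways that cannot be compared.

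**Working it through.** **1. The plan's own figure.** The stated inputs are 121 per group, a 0.5-portion difference, 90 % power and two-sided 5 %. No SD is stated. Solving n = 2(1.960 + 1.282)² SD² / 0.5² for the SD at n = 121 gives SD = 0.5 × √(121/2) / 3.242 = 1.20 portions. With SD 1.2 the formula gives 122 per group, and power at 121 is 90.0 %. So 121 is consistent with an unstated SD of about 1.2, but cannot be confirmed from the stated inputs.

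**2. Which n to use.** The article anticipates 30 % loss, and 121/(1 − 0.30) = 173, which fits the planned 180-200 per arm. The check therefore takes 121 as the number analysed.

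**3. Effect size.** 0.5/1.2 = 0.417 SD. Multiplied by 1.81 this is a log odds ratio of about 0.755. It is borrowed from fruit and vegetables as a yardstick, because the article gives no target for other items.

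**4. Power, pupils taken as independent, 121 per group, seven levels, two-sided 5 %.**

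| Simulation (assumed inputs) | Fisher | Rank test | Score model with baseline answer |
|---|---|---|---|
| Proportional-odds shift, log OR 0.8, three category distributions | 74-78 % | 93-94 % | not run |
| Latent normal shift 0.42 SD, two distributions | 61-64 % | 86-89 % | 89-97 % |
| Latent normal shift 0.30 SD, two distributions | 32-34 % | 59-62 % | 65-77 % |

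The last column assumes latent baseline-to-end correlations of 0.3 and 0.6. Under no effect, Fisher's test rejected in about 3-6 % and the rank test in about 4-6 %, so the gap does not come from unequal error rates. At 180 per group and 0.42 SD the results were 82-83 % (Fisher), 96-97 % (rank) and 98-100 % (with baseline answer).

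**5. What happens when schools differ.** Four schools, 121 per arm, no true effect, and a school effect entering the end-of-intervention answer. Share of trials wrongly significant at a nominal 5 %:

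| Intraclass correlation (assumed) | Fisher | Rank test | Score model with baseline, no school term |
|---|---|---|---|
| 0.01 | 8 % | 12 % | 13 % |
| 0.02 | 9 % | 17 % | 21 % |
| 0.05 | 20 % | 31 % | 36 % |

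The more sensitive test is also more sensitive to school differences. Respecting order without allowing for school makes the false-positive rate worse.

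**The case against.** The strongest reply is that the article never says sweets or soft drinks go to Fisher's test.

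- **Group membership.** Table 3 files the whole food question under primary outcomes; on that reading both items go to the mixed model and the example falls away. The label is weak evidence, since breakfast sits in the same block and the text calls it secondary. It is enough to make the assignment an inference.
- **Coding.** The sample size is stated in portions, so food answers might be scored as quantities. A scored item would go to the t-test, which in the 0.42 SD simulation had 87-89 % power, about the same as the rank test. That would still leave out baseline and school.
- **Aim.** A reader might infer that the trial risks missing a reduction in sweets that it sets out to achieve. No stated aim or outcome covers sweets or soft drinks; they appear only inside the survey question.
- **Size.** A reader might take the gap in the power table as what the repair would recover. It compares individual-level tests under independence; the power of an ordinal mixed model with two schools per arm was not computed. A reader might also cut 121 by 30 % to about 85, but step 2 shows that 121 fits the number after loss. Variance reductions of the form 1 − r² from using baseline belong to a linear model and do not carry over to a cumulative-logit odds ratio.

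All of this stands and limits reach and size. It does not remove the rule itself: the article fixes the test for remaining categorical variables, and that test suits ordered answers badly.

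**Conclusion.** The point holds as a minor, cheap improvement. For any remaining ordered item treated as categorical, the stated rule discards the category order, the baseline answer and the school. With effects near the planned standardised size and 121 independent pupils per group, Fisher's test had about 61-78 % power against 86-94 % for an order-respecting test. The category distributions and shifts are assumed, and the SD of 1.2 is back-calculated, so these figures are illustrative.

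The documents do not support a stronger conclusion. The named primary and secondary outcomes, including the ordered breakfast, activity and screen items, are assigned to mixed models, so no main conclusion depends on this rule. Whether sweets and soft drinks fall under it is the likelier reading of the outcome lists, but it is not settled.

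**What to change.** 1. State which analysis group the sweets and sugared-soft-drink items belong to, and bring Table 3 and the outcome lists into line.
2. Replace the Fisher rule for ordered items with wording such as: remaining efficacy items with ordered response categories will be analysed on the full ordinal scale by a cumulative-logit mixed model for the end-of-intervention answer, with arm and baseline answer as fixed effects and school as the cluster, reporting the common odds ratio and its 95 % confidence interval. Exact tests are kept for truly nominal items only.
3. Do not substitute a plain rank test that ignores school.

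The cost is a few sentences and a little more modelling in the software already named; no new data or pupils are needed. There are two downsides. The proportional-odds assumption has to be checked and reported, and with two schools per arm inference remains fragile whichever model is used.

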**Methods/Design:**

In Spain, the research team performed a cluster randomised controlled intervention over 2 academic years (2013–2015) in which 2 high-schools were designated as the control group and 2 high-schools were designated as the intervention group, with a minimum of 121 schoolchildren per group.

From the intervention group, 5 adolescents with leadership characteristics, called “Adolescent Challenge Creators” (ACCs), were recruited. These 5 ACCs received an initial 4 h training session about social marketing principles and healthy lifestyle theory, followed by 24 sessions (1.30 h/session) divided in two academic years to design and implement activities presented as challenges to encourage healthy lifestyles among their peers, the approximately 180–200 high-school students in the intervention group. During the design of the intervention, it was essential that the ACCs used the 8 social marketing criteria (customer orientation, behaviour, theory, insight, exchange, competition, segmentation and methods mix). The expected primary outcomes from the Spanish intervention will be as follows: increases in the consumption of fruits and vegetables and physical activity practice along with reductions in TV/computer/game console use. The secondary outcomes will be as follows: increased breakfast consumption, engagement with local recreation and reduced obesity prevalence. The outcomes will be measured by the Health Behaviour in School-aged Children Study (HBSC) survey at baseline and at the end of the intervention.

In the control group, no intervention was implemented, but the outcome measurements were collected in parallel with the intervention group.

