### Spanish study design

The “Som la Pera” intervention is a school cluster randomised controlled trial. The participating Spanish city was Reus (Catalonia). Local authorities have already identified public high-schools that they agree serve low-income neighbourhoods that are considered disadvantaged areas. From the 9 public high-schools identified in these neighbourhoods, 4 high-schools were randomly selected. The randomisation code was computer generated. The high-schools were assigned to the control or intervention arm at a ratio of 1:1 via an interactive electronic response system hosted by the Nutrition and Health Technology Centre (CTNS) in Reus, Spain. The unit responsible for the randomisation took no further part in the study. Because the researchers know the names of the four high-schools, allocation concealment was not performed. The project consists of five main phases, as shown in Fig. 1. The first phase included the randomisation and allocation of the high-schools in the disadvantaged area into the two intervention and two control high-schools. High-school teachers from the randomised intervention group selected the five adolescents according to their knowledge of the students by considering leadership characteristics and English level (because the students will participate in EYTO European meetings), 2 adolescents from one high-school and 3 from the other high-school. These 5 adolescents will be referred to in this protocol as the Adolescent Challenge Creators (ACCs). The study characteristics are summarised in Table 1.

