#### Additional information

This study followed the SPIRIT [37] and TIDieR protocol description recommendations [38] as presented in Additional file 1 and Additional file 2. The participation, schedule of enrolment, interventions and assessment are presented in Table 4. Finally, a cluster CONSORT checklist and flow diagram were used to summarise the description of study when the study and analysis were completed [39].

**Table 4 Tab4:** Spanish EYTO participation, schedule of enrolment, interventions and assessment

	Study period							
	Enrolment	Allocation	Post-allocation					
	Phase 1				Phase 2			Phase 3
Timepoint	-t_1_	a0	t_1_	t_2_	t_3_	t_4_	t_5_	t_6_
	May 2014_(after CEIC approval)_	May 2014	May 2014	May 2014	May 2014	September 2014	September 2014	October 2014
	High-Schools of low income in Reus are included in this phase.	4 high-school are randomly chosen, 2 in the intervention and 2 in the control group	Control High-school meeting, Separate Intervention high-school meeting and 5 ACC selection	Social marketing, health promotion and communication training for 5 ACCs	Each participant answered the HBSC Survey.	Implementation of challenges by the 5 ACCs with help of stakeholders for their peers.	Preparation of the ACC presentation of the first academic Spanish intervention at the EYTO meeting in London.	Meeting of 5 ACCs from the 4 EYTO participating countries in London to pool designed activities and exchange ideas. Successful intervention activities can be re-implemented.
	Randomisation is performed.			Design of the intervention. Information and informed consent signed	Implementation of interventions by the 5 ACCs for their peers in high-school for 12 weeks.			
Enrolment:	360–400 adolescents from low-income neighbourhoods.							
Eligibility screen	X		X					
Informed consent								
[List other procedures]								
Allocation	180–200 from intervention group and 180–200 from control group							
Intervention			Training of 5 ACCs to design activities		HBSC Survey Implementation of activities during 12-week period	Implementation of social event challenges in the community and local markets for their peers		Evaluate the activities performed during 12-week period (1^st^ academic year)
Control			This group did not receive any interventions		HBSC Survey			
Assessments: List baseline variables	X	X	X				X	X

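### Fisher's exact test and Student's t-test, fixed for the residual efficacy variables, treat pupils as independent although four schools were randomised, so their p-values are too small

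*Protocol article*

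**What the plan says.** Under Spanish study design, the article says that the "intervention is a school cluster randomised controlled trial". The same section says: "The high-schools were assigned to the control or intervention arm at a ratio of 1:1". The abstract gives the count: "2 high-schools were designated as the control group and 2 high-schools were designated as the intervention group".

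The Statistical analysis plan section uses two tiers of method. Primary and secondary outcomes are assigned to generalised linear mixed models. For what remains it says: "For the rest of the efficacy variables, we will use Fisher’s exact test for the categorical variables", with Student's t-test for the continuous variables. The significance level is two-sided 5 % throughout. For the second tier the section mentions no cluster adjustment, school-level summary or ICC.

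For school size, Table 4 plans "180–200 from intervention group and 180–200 from control group". The sample size paragraph works "with a sample size of 121 adolescent schoolmates per group" and anticipates 30 % loss to follow-up.

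**The concern.** Fisher's exact test and the two-sample t-test are valid when each observation is independent of the others. Here allocation was by school. Pupils in one school share teachers and peers and, in the intervention arm, the same in-school challenges. Two pupils from one school will therefore tend to resemble each other more than two from different schools. With only two schools per arm, chance differences between schools have almost no opportunity to cancel out.

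A pupil-level test counts all pupils as separate evidence and compares the arms against a standard error that leaves out variation between schools. An ordinary school difference can then be declared an intervention effect more often than the stated 5 %.

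This is not a detail left to a fuller plan. The text names the tests, and a model with a school effect would replace them, not elaborate them.

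**Working it through.** **1. Are these pupil-level tests?** The article does not say so in words. With two schools per arm, the most extreme school-level 2 x 2 table is 2/0 against 0/2. Of the six ways to split four schools two and two, two are that extreme, so the smallest two-sided Fisher p is 2/6 = 0.33. A school-level Fisher test could never reach 5 %. A t-test on four school means is possible in principle, but the text gives no sign of one and pairs the t-test with Fisher's test in one sentence. The pupil-level reading is the only workable one.

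**2. The plan's own figure.** The article gives no standard deviation, so 121 per group cannot be strictly reproduced. Back-solving with a 0.5 portion difference, 90 % power and two-sided 5 %: SD = 0.5 x sqrt(121/2) / (1.960 + 1.282) = 1.20. So 121 fits an ordinary two-sample calculation with no design effect. It also fits the planned enrolment, since 121/0.70 = 173 against 180-200. It serves here only as a check on school size.

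**3. Completers per school.** Enrolment of 180-200 per arm over two schools gives 90-100 per school. After 30 % loss: 90 x 0.70 = 63 and 100 x 0.70 = 70. The sample size figure gives a similar number: 121/2 = 60.5.

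**4. Type I error.** With m pupils per school, the variance of an arm mean is inflated by DE = 1 + (m - 1) x ICC. A nominal 5 % test that ignores this has true size 2 x (1 - Phi(1.96 / sqrt(DE))). The ICCs are assumptions.

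| ICC (assumed) | DE, m = 63 | 1.96/sqrt(DE) | True size | DE, m = 70 | 1.96/sqrt(DE) | True size |
|---|---|---|---|---|---|---|
| 0.01 | 1.62 | 1.540 | 12.4 % | 1.69 | 1.508 | 13.2 % |
| 0.02 | 2.24 | 1.310 | 19.0 % | 2.38 | 1.270 | 20.4 % |
| 0.05 | 4.10 | 0.968 | 33.3 % | 4.45 | 0.929 | 35.3 % |

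At 60.5 per school the results are 12.1 %, 18.5 % and 32.6 %. Even at ICC 0.005 the size there is 8.5 %.

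**5. Check by simulation.** Two schools against two, 60 pupils each, no intervention effect:

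| ICC | t-test, normal data (20,000 runs) | Fisher's test, 30 % prevalence (4,000 runs) |
|---|---|---|
| 0 | 5.0 % | 4.0 % |
| 0.01 | 12.3 % | 10.3 % |
| 0.02 | 18.2 % | 16.6 % |
| 0.05 | 33.0 % | 29.8 % |

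The formula holds for the t-test. Fisher's conservatism removes only a little of the excess. At ICC 0 both tests behave, so the excess is due to clustering.

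**6. Effect on a single p-value.** Four schools less two arms leave 2 between-school degrees of freedom. A pupil-level p of 0.05 (statistic 1.96) becomes 2 x P(T with 2 df > 1.96/sqrt(DE)). For m = 63 to 70 this is 0.263-0.271 at ICC 0.01, 0.321-0.332 at 0.02 and 0.435-0.451 at 0.05.

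**The case against.** The strongest objection is about reach. Primary and secondary outcomes go to mixed models, and Table 3 labels every block of survey items primary or secondary. The article defines no variable that clearly falls to the second tier, so the sentence may govern little. This stands, and it sets the weight of the point. It does not remove it, because the article does provide for such variables and fixes an unsuitable test for them. The boundary is also loose: the dieting item is labelled secondary in Table 3 but is not in the running-text list of secondary outcomes.

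The size also depends on ICCs the article does not give. This stands for the size. The direction needs only a positive ICC, which is to be expected for pupils within schools.

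Stronger readings are tempting but not supported:

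- A reader might infer a conflict with the intention-to-treat set, "defined as a participant who had at least baseline efficacy data", since a test of end values cannot use a pupil without one. The article does not say how missing end values are handled. These tests can be run on imputed data, and a t-test on change scores fits the wording too. Neither a complete-case analysis nor the lack of baseline adjustment is stated.
- A reader might add that confidence intervals will be too narrow. The section ties 95 % intervals to the descriptive results and attaches none to these tests.
- A reader might compute the error from 90-100 enrolled pupils per school and get 15-17 %, 24-26 % and 40-42 %. With the anticipated 30 % loss, the completer figures are the fairer ones.

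**Conclusion.** The concern holds for the residual efficacy variables. The article fixes two tests that ignore the randomised unit, and their p-values will be too small whenever the ICC is positive. With 63-70 completers per school, the true type I error of a nominal 5 % t-type test is about 12-13 %, 19-20 % and 33-35 % at assumed ICCs of 0.01, 0.02 and 0.05, and slightly less for Fisher's test. This rests on the assumed ICCs, equal school sizes and the anticipated 30 % loss falling evenly.

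It should not be read as saying that the primary or secondary analyses use these tests; they do not. No primary or secondary conclusion depends on this sentence. The correction is worth making, but it ranks below the changes that the trial cannot do without.

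**What to change.** Delete the sentence that assigns Fisher's exact test and Student's t-test. For any efficacy variable that is neither primary nor secondary, choose one of these in advance:

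- a mixed model suited to the variable type that explicitly includes a school random effect and uses small-sample degrees of freedom;
- a comparison of the four school-level means or proportions;
- descriptive reporting by arm and school, without p-values.

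A bare reference to the mixed model already planned for the main outcomes would not be enough, because the section names no random effects for it.

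The edit costs one sentence and a little programming. The statistical cost is larger p-values and little power. As an illustration, take 121 per arm, the back-solved SD of 1.20 and a t-test on 2 degrees of freedom. Power for a 0.5 portion difference is then about 31 %, 25 % and 16 % at ICCs of 0.01, 0.02 and 0.05. That reflects having four schools, and it makes descriptive reporting a reasonable choice for lower-tier variables.

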**Fig. 1 Fig1:**
[figure not shown]
Spanish Intervention Schedule of the European Youth Tackling Obesity (EYTO) Project

**Table 1 Tab1:** General study characteristics

Arm	High school information	Assigned interventions	Population	Primary and secondary outcomes
Intervention group	High-school A	The intervention group will receive an intervention consisting of challenges designed by 5 ACCs. These activities must have social marketing criteria.	High-school A	Primary outcome: consumption of fruits and vegetables, physical activity practice, and TV/computer/game console use. Secondary outcomes: breakfast consumption, engagement with local recreation and obesity prevalence
The intervention group received challenges designed by ACCs that promote healthy lifestyles.	Economically disadvantaged		Students from high schools from low-income neighbourhoods, who are 13 to 16 years of age:	
	Size: 3 classes/level		a) 3 to 5 ACCs	
	Public		b) 80-100 adolescents	
	Reus			
	High-school B		High-school B	
	Economically disadvantaged		Students from high schools from low-income neighbourhoods, 2who are 13 to 16 years of age:	
	Size: 4 classes/level		a) 2 to 5 ACCs	
	Public		b) 80-100 adolescents	
	Reus			
Control group	High-school A	No intervention is assigned for this group.	High-school A	The same outcomes were measured with the same tools and over the same time frame as in the intervention group.
The control group no received challenges to promote healthy lifestyles.	Economically disadvantaged		Students from high schools from low-income neighbourhoods, who are 13 to 16 years of age:	
	Size: 3 classes/level		b) 80-100 adolescents	
	Public			
	Reus			
	High-school B		High-school B	
	Economically disadvantaged		Students from high schools from low-income neighbourhoods, who are 13 to 16 years of age:	
	Size: 4 classes/level		b) 80-100 adolescents	
	Public			
	Reus			

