		Outside school hours: How often do you usually exercise in your free time so much that you get out of breath or sweat?	Every day, 4–6 times a week, 2–3 times a week, once a week, once a month, less than once a month, never.
		Outside school hours: How many hours a week do you usually exercise in your free time so much that you get out of breath or sweat?	None, about half an hour, about 1 h, about 2 to 3 h, about 4 to 6 h, about 7 h or more.
Sedentary behaviour	Sedentary behaviour	About how many hours a day you usually watch television (includes DVD and videos) in your free time?	Weekdays: None at all, about half an hour a day, about 1 h a day, about 2 h a day, about 3 h a day, about 4 h a day, about 5 h a day, about 6 h a day, about 7 or more hours a day.
(primary outcomes)			Weekends: None at all, about half an hour a day, about 1 h a day, about 2 h a day, about 3 h a day, about 4 h a day, about 5 h a day, about 6 h a day, about 7 or more hours a day.
		About how many hours a day do you usually play games on a computer or games console (PlayStation, Xbox, GameCube, etc.) in your free time?	Weekdays: None at all, about half an hour a day, about 1 h a day, about 2 h a day, about 3 h a day, about 4 h a day, about 5 h a day, about 6 h a day, about 7 or more hours a day.
		About how many hours a day do you usually use a computer for chatting on-line, internet, emailing, homework, etc. in your free time?	Weekends: None at all, about half an hour a day, about 1 h a day, about 2 h a day, about 3 h a day, about 4 h a day, about 5 h a day, about 6 h a day, about 7 or more hours a day.
Self-confidence	Weight control and body image	At the present, are you on a diet or doing something else to lose weight?	No, my weight is fine; No, but I should lose some weight; No, because I need to put on weight; Yes.
(secondary outcomes)			
Body mass index (secondary outcomes)	Perceived obesity and overweight prevalence	How much do you weigh without clothes?	Free space for answer.
		How tall are you without shoes?	Free space for answer.

Items obtained from the Health Behaviour in School-Aged Children (HBSC) 2009/2010 Ref. [35]

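### Three unranked primary outcome domains share one two-sided 5 % level, with no testing order, adjustment or rule for what counts as success

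*Protocol article*

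**What the plan says.** The Abstract, Table 1 and the section on primary and secondary outcomes agree on three primary domains. Table 1 lists "Primary outcome: consumption of fruits and vegetables, physical activity practice, and TV/computer/game console use". The outcomes section expects "increases in the consumption of fruits and vegetables and physical activity practice, along with reductions in TV/computer/game console use". None is placed above the others.

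The Statistical analysis plan section sizes the trial on one of the three: 121 adolescents per group, 90 % power, a difference of half a portion of vegetables or fruits, two-sided 5 %. It then applies mixed models to primary and secondary outcomes alike and closes with "The significance level is fixed at a bilateral level" of 5 %. It mentions no order of testing, no adjustment and no success rule.

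Table 3 marks whole blocks of the survey as primary and names no key item or score in any of them:
- **Eating habits:** one frequency question covering several foods ("How many times a week do you usually eat or drink (fruits, vegetables, sweets, coke or other soft drinks that contain sugar"), plus breakfast.
- **Physical activity:** three questions, the first asking "on how many days were you physically active for a total of at least 60 min per day".
- **Sedentary behaviour:** three questions, on television ("About how many hours a day you usually watch television (includes DVD and videos) in your free time"), games and computer use.

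The text classes breakfast differently from the table: "The secondary outcomes were as follows: increased breakfast consumption, engagement with local recreation and reduced obesity prevalence".

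**The concern.** With three co-equal primaries and one 5 % level, a reader following the section as written would test each domain at 5 %. Nothing then stops a single significant domain from being presented as success on the primary outcome, and the error rate for that claim is higher than 5 %.

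The open choice of items within each domain adds to the problem. If the item or score that represents a domain is not fixed beforehand, it can be chosen after the results are seen. The breakfast contradiction shows that the boundary of the primary family is itself unsettled. What is at stake is how much weight a positive primary finding can carry.

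**Working it through.** **The plan's own figure.** The only related figure is 121 per group. The standard deviation is not given, so 121 cannot be strictly reproduced. With n = 2 × [SD × (1.960 + 1.282) / 0.5]²:
- Assumed SD 1.2 gives n = 121.05, which matches if 121 means evaluable participants.
- Assumed SD 1.0 gives n = 84.06, and 84.06 / 0.7 = 120.1, which matches if 121 already allows for the 30 % loss.

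Either way the calculation uses the full two-sided 5 % for one outcome, so it contains no allowance for three primaries.

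**Inputs for the error rate.** The level is 0.05 two-sided (Statistical analysis plan section), and there are three domains (Abstract, Table 1, outcomes section). Three things are assumed: any one significant domain counts as success, no outcome truly differs, and each single test holds its 5 %.

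**Any false positive, three tests.** If independent, 1 − 0.95³ = 14.3 %. Simulation with equally correlated normal test statistics (400,000 draws) gives:

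| Correlation | Three tests |
|---|---|
| 0.3 | 13.7 % |
| 0.5 | 12.5 % |
| 0.7 | 10.9 % |

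**False benefit only.** A two-sided 5 % test errs in the favourable direction with probability 2.5 %. Three independent tests give 1 − 0.975³ = 7.3 %. Positive correlation lowers this.

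**Item count.** Table 3 gives fruit and vegetables (2), activity (3) and sedentary questions (3), which makes 8. The count is 9 if the four sedentary answer sets shown are counted (television weekday, television weekend, games, computer), or if breakfast is added to the 8.

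**Assumed upper case, nine items each tested at 5 %.** If independent, 1 − 0.95⁹ = 37.0 %. The simulated values are 32.6 % at correlation 0.3, 26.9 % at 0.5 and 20.3 % at 0.7. For a false benefit alone, independence gives 1 − 0.975⁹ = 20.4 %.

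**What a correction would cost.** Splitting 5 % equally over three gives 0.05 / 3 = 0.0167 per test and a family-wise error of 1 − (1 − 0.0167)³ = 4.9 % if independent. At assumed SD 1.2 and 121 evaluable per group, power for half a portion falls from 90 % to 80 %. Restoring 90 % would need 156 evaluable per group. A fixed order keeps 0.05 for the first test, so the 121 for fruit and vegetables is unaffected.

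**The case against.** The strongest reply is that this is a condensed article, and that multiplicity rules and item scoring commonly sit in a fuller plan. On that view silence is not a decision to test everything unadjusted. This stands in part: the article does not say that each Table 3 item will be tested, or that any one of them suffices. It does not remove the point, because the article itself fixes the error level, and fixes it as one value over three co-equal primaries. The breakfast contradiction is also in the text as printed and is not an omission.

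A second reply is that the outcomes are joined by words such as *and* and *along with*, which could mean that all three must improve. If that were the rule, no adjustment would be needed. The article does not state it, so the figures above are conditional on the other reading.

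Three stronger readings are tempting and are not supported:
- **A false-positive primary is likely.** Even the assumed upper case stays at 37 %, below one half, and the three-domain figure is 11 to 14 %.
- **There are nine primary tests.** The outcomes are named as domains. Nine is a count of what Table 3 would permit, taken from a table whose weekday and weekend answers are incomplete as shown for games and computer use.
- **The 14 % is the chance of a false benefit.** The tests are two-sided, so that figure also counts false results in the harmful direction.

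**Conclusion.** The point holds for three unranked primary domains at one two-sided 5 % level. If any one significant domain counts as success, the chance of at least one false-positive primary is about 11 to 14 % (correlation 0.7 down to 0), which is two to three times the nominal 5 %. The chance of a false benefit is about 7 % if the tests are independent, nearly three times the nominal 2.5 %. The 20 to 37 % range applies only if about nine items were each tested separately, which the article neither states nor rules out. All figures assume that no outcome truly differs and that each single test holds its level. Separately, Table 3 and the text contradict each other on breakfast.

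**What to change.** Before the outcome comparison:

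1. Name one item or score for each primary domain. For fruit and vegetables, say how it relates to the half portion used for sizing, since Table 3 records frequency categories. For screen use, confirm which weekday and weekend answers were collected before defining a score. The article gives no ground for preferring one activity question, so give the reason for the choice.
2. Test fruit and vegetable consumption first at two-sided 5 %, because the trial is sized on it. Then test physical activity, then screen use, each only if the previous test is significant. Alternatively, use Holm across the three.
3. Label the remaining items exploratory, and mark breakfast as secondary in Table 3 to match the text.
4. State the date of the change relative to the end survey, which Table 4 places in February 2015. Table 4 places the data analysis in September 2015.

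The text change is short, but the item definitions need some work. Under the fixed order, activity and screen-use claims become conditional on the earlier tests, and the first test loses nothing. Under Holm no claim depends on the order, but each test loses some power. At worst the loss equals that of the equal split, 90 % to 80 % for half a portion under the assumed SD of 1.2 with 121 evaluable per group.
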